#### Statistical analysis: additional analyses

Mixed-effects models with an unstructured covariance matrix will be used to estimate the primary outcome of brain volumes measured at 3 and 12 months postinjury; the models will include subjects as random effect and dynamic CA indices, time, and dynamic CA indices 
×
 time interaction as fixed-effects factors. Other covariates or potential confounders (e.g., age, sex, dynamic CA indices and others) will be included in these mixed-effects models. Conditional Akaike information criteria and other goodness of fit criteria will be applied to select the parsimonious mixed-effects model. Similar modeling and data analysis will be applied with DTI measure of white matter integrity as a dependent variable. In the secondary analysis, mediation models will be performed to study the overall association of Δ CA and CBF variables (both global CBF measured by 2D color-coded duplex ultrasonography and regional CBF measured by ASL) with the outcome of Δ NIHTB_CB fluid composite score and to estimate the extent to which this association is mediated by Δ brain volumes or white matter integrity. We will repeat the above procedures for the DMN connectivity from rs-fMRI to explore if the associations between cerebrovascular function recovery, cognitive and functional outcomes are mediated by changes in brain neural network connectivity. Secondary outcomes, including changes in cognitive outcomes, R-GOSE score and PROMIS measures, will be analyzed followed by similar analytical approaches, and evaluated both total effects of Δ CA/CBF variables and mediation effects of Δ brain volumes. No adjustments for multiple comparisons will be made for all secondary analyses, which are considered as exploratory analyses. Assumptions and diagnosis for mixed-effects models will be carefully evaluated. Missing data will be imputed using multiple imputation by chained equations and pattern mixture approaches as needed and evaluated by the sensitivity analyses.

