#### Imaging protocol

The initial clinical head CT data from the emergency room will be downloaded. Lesion characteristics will be documented in REDCap, including intracranial pathologies, subarachnoid hemorrhage, extra-axial or subdural hemorrhage, as well as findings related to cisterns and surgeries based on NIH Comment Data Elements. MRI scans will be collected at 3 months (±2 weeks) and 12 months (±1 month) post-injury, and analyses will account for the impact of lesion location and size on a subject-by-subject basis.

MRI data will be collected on a Siemens Prisma 3 T scanner: (1) 3D Multi-Echo T1-weighted Magnetization-Prepared-Rapid-Acquisition-of-Gradient-Echo (3D ME-MPRAGE) sequence (32) will be used to measure brain volumes. (2) 3D T2 FLAIR sequence (32) will be used to assess white matter hyperintensity volume and location (33). (3) 3D Multi-Echo Gradient Recalled Echo (3D ME-GRE) (32) will be used to visualize and quantify microbleeds and hemorrhage (34).

(4) 3D Pseudo Continuous Arterial Spin Labeling (3D PCASL) sequence will be used to measure regional CBF (35, 36). (5) Diffusion tensor imaging (DTI) with multiple b values, including 114 diffusion-weighted image volumes, will be used to assess white matter microstructural integrity (37). (6) Resting-state fMRI (rs-fMRI) will be used to assess brain network functional connectivity with a focus on the DMN (Default Mode Network) (38–42).

Each MRI scan will be visually reviewed within three business days. Preliminary processing will generate maps including FreeSurfer T1 segmentation, R2*, SWI, QSM, ASL perfusion, DTI FA/MD, fiber tracking, and resting-state fMRI SNR/connectivity. [name] (MRI physicist) or his trainee will assess image quality. Inferior image quality is often due to motion, acquisition errors, or system issues. Imaging sequences with inferior quality will be marked, and rescanning will be attempted if feasible. Poor-quality sequences will not be included in final analyses.

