##### TBI lesion characterization

A neuroradiologist will visually review T1, T2 FLAIR, and GRE images (the R2*, SWI and QSM maps genrated from the multi-echo GRE images as well) to assess “lesion load.” Participants with large lesions (>5 cm^3^ subcortical, >50 cm^3^ cortical) will be excluded from automated analysis, but DTI metrics and CBF will be examined on these lesions. Case-by-case approaches will address large lesions.

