##### Volumetric data processing

3D T1 MPRAGE images will undergo a series of FreeSurfer-based processing procedures to generate cortical and subcortical morphometrics (43, 44). To improve the cortical surface reconstruction, T2 FLAIR data will be incorporated into FreeSurfer’s reconstruction pipeline (45). To reduce the potential impact of brain lesions due to TBI on cortical surface reconstruction, we will visually inspect each segmentation and manually label and remove vertices on the cortical surfaces caused by the lesions (45). The scans which fail to complete the processing pipeline or require major manual edits will be excluded for further analysis (45). The corrected maps and regional volumes will be used for further post-processing.

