#### Statistical methods: outcomes

For the primary analysis, multiple linear regression models will be performed to examine the associations of dynamic CA indices on the primary outcome of NIHTB_CB fluid composite score at 1 year post injury, adjusted by potential confounders (i.e., initial GCS, posttraumatic amnesia, head CT scan, age, sex, etc.). The parsimonious model will be selected via the automatic model selection algorithms, including forward, backward, and stepwise selection. Multicollinearity will be evaluated using variance inflation factors, and the issue of overfitting will be assessed through 10-fold cross-validation. For the secondary analyses, secondary outcomes, including CA/CBF and other continuous cognitive measures, R-GOSE score as well as health-related PROMIS measures at 1-year postinjury, will be analyzed separately through the same analytical approach. Sensitivity analyses of the outcomes will be performed to assess the robustness of the findings, including model diagnostics, outlier assessments, distributional assumptions, and missing data. Data transformation will be made if the normality assumption is violated.

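### The imaging mixed models list the exposure as its own covariate, name no injury-severity confounder and let fit criteria pick the final model, so severity could confound the CA–brain volume and CA–DTI associations

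*Protocol article*

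**What the plan says.** The section on additional analyses sets out the models for the imaging aim. The dependent variable is the "primary outcome of brain volumes measured at 3 and 12 months postinjury", and DTI measures of white matter are to be modelled in a similar way. On the fixed and random terms it says "the models will include subjects as random effect and dynamic CA indices, time, and dynamic CA indices", the last of these being the interaction with time. The next sentence reads "Other covariates or potential confounders (e.g., age, sex, dynamic CA indices and others) will be included in these mixed-effects models". The model is then reduced: "Conditional Akaike information criteria and other goodness of fit criteria will be applied to select the parsimonious mixed-effects model".

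For the cognitive outcome, the section on statistical methods for outcomes has the CA indices "adjusted by potential confounders (i.e., initial GCS, posttraumatic amnesia, head CT scan, age, sex, etc". The power section lists six control variables: those five and education.

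On lesions, the imaging protocol promises that "analyses will account for the impact of lesion location and size on a subject-by-subject basis", and the lesion section adds "Participants with large lesions (>5 cm^3^ subcortical, >50 cm^3^ cortical) will be excluded from automated analysis". The volumetric section ends with "The corrected maps and regional volumes will be used for further post-processing". Head size and intracranial volume are not mentioned anywhere in the article.

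**The concern.** Three features of the imaging model combine.

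- **The exposure appears twice.** It is first an effect of interest and then an example of an additional covariate. The sentence does not say whether another CA index, another time point or simply another variable was meant.
- **Severity is not named.** The cognitive model treats GCS, amnesia and head CT as confounders of acute CA. The imaging model studies CA in the same patients, but apart from the exposure itself its named examples are age and sex.
- **Selection is by fit.** Criteria that reward parsimony judge a covariate by how well it predicts the outcome, not by how much its removal shifts the CA coefficient. A confounder entering as one of the unnamed covariates has no protection.

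The third aim is at stake. A more severe injury can plausibly both impair autoregulation and cause tissue loss. Unless severity is held in the model, an association of CA with volume or DTI may reflect shared severity rather than a link between CA and neurodegeneration.

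**Working it through.** **The plan's own figure.** The article gives no power or sample size for the imaging models. Its one power figure concerns the cognitive regression: N = 117, R² increase 0.053, two tested and six control variables, control R² 0.35. It reproduces: f² = 0.053/(1 − 0.35 − 0.053) = 0.0888, noncentrality 117 × 0.0888 = 10.39, df 2 and 108, power 0.8195 against the stated 82%. Enrolment is 117/0.9 = 130. Nothing below changes these numbers.

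**Step 1: what the repeated term does.** A design with an intercept and the same CA index entered twice has three columns and rank 2. The second entry is redundant, adjusts for nothing and does not bias the CA estimate. If instead each CA index is adjusted for the others, the model can be fitted, but each coefficient then means the effect of that index given the rest. The text does not say which is intended.

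**Step 2: named covariates side by side.**

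| Covariate | Cognitive model (power or outcomes section) | Imaging models |
|---|---|---|
| Age, sex | named | named |
| Initial GCS | named | not named |
| Posttraumatic amnesia | named | not named |
| Head CT | named | not named |
| Education | named (power section) | not named |
| Dynamic CA indices | exposure | exposure, and again as covariate |

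**Step 3: size of the possible bias.** The inputs are n = 90 (analysable TBI patients, power section), two-sided 5% (statistical analysis plan section) and correlations of severity with CA and with volume, which are assumptions. With no true CA effect and severity omitted, the spurious correlation is

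r(CA, volume) = r(CA, severity) × r(severity, volume).

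The rejection rate by Fisher's z uses t = atanh(r) × √(90 − 3) and equals 1 − Φ(1.96 − t) + Φ(−1.96 − t).

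| Assumed correlation of severity with each | Spurious r | False-positive rate |
|---|---|---|
| 0 and 0 | 0 | 5% |
| 0.2 and 0.2 | 0.04 | 6.6% |
| 0.3 and 0.3 | 0.09 | 13.4% |
| 0.4 and 0.4 | 0.16 | 32.5% |
| 0.5 and 0.5 | 0.25 | 66.4% |

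Unequal pairs follow the same rule: 0.2 and 0.4 give 0.08 and 11.6%. This is a single cross-sectional correlation, not the two-time-point mixed model. It shows the mechanism and the order of size.

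**Step 4: head size, volume outcomes only.** If intracranial volume explains a share R² of between-subject variance in volume (assumption), adjusting for it multiplies the standard error of the CA main effect by √(1 − R²): 0.84, 0.71 and 0.55 for R² of 0.3, 0.5 and 0.7. Head size does not change between 3 and 12 months in an adult, so an additive head-size effect largely cancels from CA × time. Sex, already named, may absorb part of the rest. The gain therefore falls mainly on the cross-sectional term.

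**The case against.** The strongest reply is that the covariate list is open. It is given as examples and ends by allowing others, and a journal article may leave the full list to an analysis plan that is not shown. That stands against a stronger reading that a reader might infer, namely that the imaging models adjust for age and sex only and that their results will be confounded and imprecise. The article does not exclude severity or head size, so confounding is a possibility and not a consequence of the text. The open ending does not settle the matter, though: the article itself fixes a fit-based selection rule, under which an unnamed severity term need not survive.

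A reader might also infer that the duplicated exposure biases the CA estimate. It does not (step 1). Adjusting one CA index for another, or follow-up CA for acute CA, could even be deliberate. What remains is that the sentence does not say so.

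Nor is lesion burden ignored. The article commits to accounting for lesion location and size, has lesion load reviewed by a neuroradiologist and takes large lesions out of automated analysis. This covers injury burden in part. It does not replace GCS or amnesia, and excluding participants with large lesions is not covariate adjustment. The same point limits the remedy: MRI is first done at 3 months, after the acute CA measurement, so forcing MRI lesion volume into every model could remove part of the association under study.

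Finally, every correlation in step 3 is assumed, and low values give little or no inflation. That is correct, and it is why the result is a range starting at 5%.

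**Conclusion.** The point holds as a badly fixed analysis rule. The covariate sentence contains a visible error, it does not carry over the article's own severity confounders to a second analysis of CA in the same patients, and the selection step leaves any unnamed confounder unprotected. The CA–volume and CA–DTI associations could be confounded by severity. Under the assumptions of step 3 (severity omitted, no true CA effect, equal correlations of 0 to 0.5, n = 90), the false-positive rate lies between 5% and about 66%. The documents do not allow a narrower statement.

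The head-size part is secondary. It concerns the precision of the cross-sectional CA effect on volumes, with a standard error lower by 16% to 45% if head size explains 30% to 70% of between-subject variance and sex has not already absorbed some of that. It says little about change over time and does not extend to DTI. The repeated exposure is a drafting error that needs correcting but is not itself a source of bias.

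**What to change.** In the section on additional analyses:

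1. Delete the second mention of dynamic CA indices, or state which other index or time point is meant.
2. Prespecify age, sex, education, initial GCS, posttraumatic amnesia and acute head CT findings as covariates kept in every imaging model, for volumes and for DTI, whatever the AIC. Limit the fit criteria to the other terms.
3. Where CA × time is the target, consider severity × time as well, since a severity main effect alone does not address confounding of change.
4. For volume outcomes, add intracranial volume, noting that it helps mainly the cross-sectional CA main effect.
5. Put MRI lesion volume in a sensitivity analysis. This is consistent with the commitment in the imaging protocol and avoids conditioning the main analysis on a measure taken after the acute exposure.

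The cost is wording and a few degrees of freedom. The severity variables already appear in the cognitive model. Intracranial volume would have to be derived from the planned T1 images, a step the article does not state.

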## Background and rationale

Nonfatal traumatic brain injury (TBI) stands as a prominent etiology of adult disability, presenting substantial morbidity for the victims, their families, and society at large, with several negative impacts, including cognitive impairment (1, 2). Moderate–severe TBI (msTBI), defined as a Glasgow Coma Scale (GCS) score of 3–12 on admission carries the largest burden of morbidity and mortality (2), with notable variability in clinical outcomes following msTBI. Cognitive impairment, including impaired memory, slow processing speed, and diminished attention span, is particularly prevalent after msTBI (3–5). Although some recovery typically occurs within the first year post-injury (3), accurately predicting long-term cognitive outcomes remains challenging.

This challenge is partly due to the high pathophysiological heterogeneity of TBI, particularly the occurrence of acute cerebrovascular injury that is common following msTBI (6). Acute cerebrovascular injury after msTBI includes vasospasm of larger cerebral arteries, trauma-induced vascular damage at smaller vessel levels, and disruption of the blood–brain barrier and endothelium due to shear (6, 7). In addition, the injury processes involve altered brain metabolism, impaired waste clearance, and neuroinflammation, leading to brain hypoperfusion, disrupted neurovascular coupling, impaired cerebral autoregulation (CA), as well as inefficient adjustments in cerebral blood flow to changes in perfusion pressure (8–10). There is some evidence suggesting that acute cerebrovascular dysfunction following TBI, as assessed by cerebral blood flow and CA by transcranial doppler (TCD), is associated with unfavorable functional outcomes in those with Glasgow Outcome Scale scores less than 3 (10). Nevertheless, a significant gap persists in the literature regarding longer-term follow-ups and comprehensive assessments of cerebrovascular function alongside cognitive function for this patient population.

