#### rs-fMRI data processing

We include rs-fMRI as an exploratory measure of changes in brain neural network connectivity after TBI (40). AFNI (Analysis of Functional NeuroImages) will be used for rs-fMRI data preprocessing (55). A robust independent component analysis based preprocessing strategy will also be assessed (40). The DMN functional connectivity has been demonstrated to be an important marker in AD (41) and TBI (56). The nodes of the DMN network as well as other networks can be extracted with the atlas published by Yeo et al. (57) in young adults or by Shirer et al. in older adults (58). The overall DMN functional connectivity, and similarly for other networks, at each time point will be calculated as the average of the pair-wise Pearson correlation coefficients of all connection pairs of DMN nodes and will be used for within-subject as well as for group comparisons (40).

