##### DTI data processing

The DTI data will be processed with FSL (48). The “topup” procedure will be used to correct susceptibility distortions (49). The Track-Based Spatial Statistics program (50) will be used to estimate fractional anisotropy, mean diffusivity, axial diffusivity, and radial diffusivity (51, 52). Free water content will be estimated with the DIPY software package (53). Probabilistic tractography will be performed to estimate brain network structural connectivity (40, 41, 54).

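### The resting-state fMRI mediation is read as neural, but its mediator is a haemodynamic signal that the vascular exposure may itself alter, so the indirect effect can be biased

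*Protocol article*

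**What the plan says.** The section on additional analyses fixes three things.

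- **Exposure:** "mediation models will be performed to study the overall association of Δ CA and CBF variables". The flow variables are "both global CBF measured by 2D color-coded duplex ultrasonography and regional CBF measured by ASL".
- **Mediator:** after brain volumes and white matter integrity, "We will repeat the above procedures for the DMN connectivity from rs-fMRI".
- **Reading:** the purpose is to see whether the associations of cerebrovascular recovery with cognitive and functional outcomes "are mediated by changes in brain neural network connectivity".

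The section on rs-fMRI data processing defines the mediator. DMN connectivity is "calculated as the average of the pair-wise Pearson correlation coefficients of all connection pairs of DMN nodes". Preprocessing is in AFNI, and an approach based on independent components is also to be assessed. The same section sets the status and the label: "We include rs-fMRI as an exploratory measure of changes in brain neural network connectivity after TBI".

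The background lists among the consequences of the injury "disrupted neurovascular coupling, impaired cerebral autoregulation (CA".

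Arterial spin labelling (ASL) and rs-fMRI belong to the same MRI protocol, at 3 and 12 months. The DTI section adds: "Probabilistic tractography will be performed to estimate brain network structural connectivity". The additional analyses name white matter integrity as a mediator but do not mention this structural network measure.

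**The concern.** In a mediation analysis the mediator should be measured in a way that the exposure does not disturb. Here the exposure is vascular and the mediator is a correlation of haemodynamic signals. In patients whose neurovascular coupling is disturbed, a change in autoregulation or flow may change the measured DMN correlation with no change in neural connectivity. The exposure-to-mediator path then contains a measurement component, and the indirect effect inherits it.

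Two explanations become hard to tell apart: vascular recovery restores networks and thereby cognition, or vascular recovery changes the fMRI signal. Because the article aims to motivate vascular-focused interventions, a pathway labelled neural could send follow-on work in the wrong direction.

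**Working it through.** **The plan's own figure.** The mediation analysis has none. The stated power belongs to the primary regression and reproduces: f² = 0.053 / (1 − 0.35 − 0.053) = 0.0888; λ = 117 × 0.0888 = 10.39; with 2 and 108 degrees of freedom, power is 0.8195 against the stated 82%. Enrolment is 117 / 0.9 = 130. Nothing below changes these.

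**Route 1: connectivity truly relates to cognition.** Let X be the exposure and N true neural connectivity, independent of X (no neural pathway). The measured mediator is M = N + cX, and the outcome is Y = bN + 0.2X + error (SD 0.9). Substituting N = M − cX gives

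Y = bM + (0.2 − bc)X + error.

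The estimated paths are therefore c (X to M) and b (M to Y given X). Their product bc is reported as the indirect effect, although the true value is zero. With b = 0.3 it is 0.06, 0.09 and 0.12 for c = 0.2, 0.3 and 0.4. Against a total effect of 0.2, that is 30%, 45% and 60% apparently mediated. If b = 0, the product is zero whatever the contamination.

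The table gives the share of simulated studies declaring mediation (both paths p < 0.05) at n = 90, the evaluable TBI number in the power section:

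| b | c = 0.2 | c = 0.3 | c = 0.4 |
|---|---|---|---|
| 0 | 2–5% across this row | | |
| 0.1 | 9% | 14% | 16% |
| 0.2 | 24% | 42% | 52% |
| 0.3 | 40% | 71% | 84% |

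With c = 0 and b = 0.3 the share is about 4%. Independent reruns differ by one to three percentage points.

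**Sample size.** Usable rs-fMRI is needed at both visits, poor-quality sequences are dropped, and participants with large lesions leave the automated analysis, so 90 may be optimistic. At an assumed n = 60 with b = 0.3, the shares are 22%, 43% and 59%. At n = 117 (controls included) they are 54%, 84% and 92%. More patients do not remove the bias; they make it more likely to reach significance.

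**Route 2: the exposure is measured with error.** Here there is no neural path at all. True vascular recovery affects cognition with standardised slope 0.5 and explains 10–50% of the variance in measured connectivity. The recorded CA or CBF value captures vascular recovery with limited reliability. At n = 90:

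| Reliability of exposure | Mediation declared |
|---|---|
| 1.0 | 4–5% |
| 0.8 | 5–13% |
| 0.6 | 7–39% |
| 0.4 | 9–67% |

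**Does adjusting for CBF help?** It depends on how the contamination travels. If CA acts on the signal through CBF (CA–CBF correlation 0.7, n = 90), adding CBF cuts false mediation from 38–74% to 4–5% when CBF is measured without error, to 7–12% at reliability 0.8 and to 12–30% at reliability 0.6. If CA acts on the signal directly and CBF is only correlated with it, little is gained: 38/66/81% remain at correlation 0.3 and 32/57/76% at 0.5, for c = 0.2/0.3/0.4.

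None of b, c, the reliabilities or the CA–CBF correlations comes from the documents.

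**The case against.** The strongest reply has four parts.

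1. **Contamination alone is not enough.** A reader might infer that vascular recovery by itself will appear as neural mediation. The calculation does not support that. The mediator-to-outcome path is tested given the exposure, so with b = 0 and a well-measured exposure the false-positive share stays at about 2–5%. A second condition is needed. This stands and limits the point. The second condition is not remote, though: a connectivity–cognition link is the premise for testing this mediator, and a single CA or CBF value is unlikely to capture vascular recovery perfectly.
2. **The analysis is already called exploratory.** That is true, and it limits the weight of the point. But the article ties that caution to multiple comparisons and Type I error. A biased path is a different problem, and the label does not address it.
3. **Preprocessing detail belongs in a fuller document.** This is fair. The absence of a named flow, CO2 or lag correction is not held against the article. The point rests on what the article does fix: exposure, mediator and interpretation. That rs-fMRI is haemodynamic is a basic property of the method, not something the article states.
4. **Other mediators are planned.** Brain volumes and white matter integrity go through the same procedure and are not fMRI signals. They give useful context but do not tell the reader how to interpret the DMN result. A reader might also want agreement with tractography before any network claim. That goes too far: function may change without structural change, so disagreement would not prove a vascular artefact.

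**Conclusion.** The point holds as a matter of interpretation and bias in one secondary, exploratory analysis. Followed as written, the plan can yield a conclusion of neural mediation when the CA-to-neural path is zero. This requires that vascular change affects the measured DMN correlation, and that either connectivity relates to cognition or the exposure is error-prone. The size is unknown. Over the assumed ranges at n = 90, the first route runs from about 2–5% of studies (no connectivity–cognition effect) to 40–84% (effect of 0.3), so no single figure from that range should be quoted alone.

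A reader might infer that the study's mediation results as a whole, or its main conclusion, are unsafe. The documents do not support that: the primary regression and its sample size do not involve fMRI, and the brain-volume and white-matter mediators are not fMRI signals.

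**What to change.** In the section on additional analyses:

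- **Label.** State the DMN result as mediation by rs-fMRI-signal (haemodynamic) connectivity, not neural connectivity. Where CBF is itself the exposure, the CBF-adjusted comparison below does not apply and this label is the main safeguard.
- **Sensitivity analysis.** Where CA is the exposure, show the DMN mediation with and without change in DMN-region ASL CBF, entered in both the mediator and the outcome model. Say that this removes only contamination carried through CBF and may also remove genuine coupling, so both versions are needed.
- **Supportive evidence.** Report the same mediation with tractography-based DMN structural connectivity, built on the tractography already planned, as context and not as a condition for a claim.

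The cost is a few extra exploratory models on data already planned, and a narrower label for one result.
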